#### Analysis of secondary outcome measures

The secondary outcomes: total number of bronchiectasis exacerbations requiring hospital admission, total number of emergency hospital admissions (all causes) will each be analysed as for the primary outcome described above. Disease-related health status (measured using the SGRQ, FEV_1_ and FVC) will be analysed using a mixed-effects model adjusted for site, stratification factors, patient characteristics and/or baseline clinical variables (to be pre-specified in the SAP). Random effects for patient will be included.

#### Exploratory and subgroup analyses

Exploratory analyses will investigate the relationship between key outcomes (exacerbations and quality of life as measured by SGRQ and QOL-B) with baseline eosinophils (single level recorded at baseline), median eosinophil level (median of last three available recordings when not on oral steroids) and baseline BSI.

Subgroup analyses of suspected aetiology comparing idiopathic and postinfectious to all other aetiologies for the key outcomes of exacerbations and quality of life (SGRQ and QOL-B) will also be carried out.

All analyses will be governed by this comprehensive SAP which will be agreed by the TSC and reviewed by the IDMEC prior to any analyses being undertaken. Unless prespecified, a 5% two-sided significance level will be used to denote statistical significance throughout.

#### Economic evaluation

Both a within-trial and model-based analysis will be undertaken. Both analyses will estimate the incremental cost per QALY gained but over different time horizons; 12 months post-randomisation (within-trial) and over the patients’ life course (economic model).

The economic analysis will take the perspective of the NHS and personal and social services. Sensitivity analyses will widen the perspective to incorporate costs incurred by participants. Intervention costs will be estimated based on the manufacturers list price of the medications and inhalers provided to participants. Primary and secondary healthcare resources use will be estimated based on responses to the Healthcare Utilisation Questionnaire (HCUQ) administered at baseline, 1, 6 and 12 months postrandomisation. These data will be combined with unit costs obtained from routine sources to estimate the total healthcare utilisation cost per participant. Additionally, patients with bronchiectasis are likely to experience AEs, treatments and hospitalisations associated with these AEs will be recorded on the eCRF and will be incorporated into the total healthcare utilisation cost per participant in a sensitivity analysis.

Direct (eg, out-of-pocket payments) and indirect (eg, time away from work) costs borne by participants will be collected via the Time and Travel questionnaire administered at 12 months postrandomisation. Similar to the healthcare costs, these study-specific estimates will be combined with routine sources to estimate the total costs incurred for each participant.

Health-related quality of life will be assessed based on responses to the EQ-5D-5L administered at baseline, 1, 6 and 12 months postrandomisation. Utility scores will be derived based on responses to the EQ-5D-5L questionnaire and the national tariff relevant at the time the study reports. QALYs will be estimated using the utility values estimated at baseline, 1, 6 and 12 months using the area under the curve method.^26^

The total cost and QALY per participant will be summarised as the average total cost and average total QALY for each of the randomised arms. All data will be presented as point estimates of incremental costs, QALYs, cost-effectiveness. The incremental cost per QALY gained will be estimated as the difference in costs divided by the difference in QALYs if one of the arms is not dominant (ie, less costly and more effective). The difference in costs and QALYs between the arms will be estimated using seemingly unrelated regression which can control for observed and unobserved characteristics that can affect costs and/or QALYs.^27^ Uncertainty in these results, estimated using the bootstrapping technique,^28^ will be presented on cost-effectiveness planes and cost-effectiveness acceptability curves (CEACs).

Given that patients with bronchiectasis are expected to take their medications over their life horizon, an economic model will be used to extrapolate the economic results beyond the 12 month treatment period. It is likely that this model will take the form of a Markov model but the specific form will be decided based on the within-trial results during the model development. Data to design and populate the model will be taken directly from the trial, routine sources (ONS and HES data), literature and clinical opinion. Cost and QALYs incurred after the first 12 months will be discounted at the recommended rate.^29^ The model will be developed using the guidance for good practice in conceptualising an economic model.^30^ Similar to the within-trial analysis, these results will be presented as point estimates of costs, QALYs and cost-effectiveness. Uncertainty in the economic model will be estimated using Monte Carlo simulations and presented as cost-effectiveness planes and CEACs.^31 32^

### Sample size calculations

The original sample size calculation was based on the number of exacerbations among a similar population in prior national audits.^15 23^ The average number of exacerbations was 2.3 per year. Restricting trial entry to those who had ≥3, the original inclusion criteria (assuming a Poisson distribution) gives an average of around 3.8. We therefore assumed, given Hawthorne effect and regression to the mean, that the placebo arm would have a lower mean exacerbation rate than this, and assumed a mean of 2.4 over 1 year. The sample size was chosen so that the trial was well powered to detect a clinically meaningful fall in mean exacerbation rates for bronchiectasis exacerbations to 1.9 year in LAMA/LABA and ICS/LAMA/LABA arms (approximately 20% reduction). This effect size is realistic when compared with the 20%–30% reduction seen in COPD trials with dual bronchodilators/triple therapy and is accepted as clinically meaningful. Although likely studying a different sub population in bronchiectasis, a recent inhaled antibiotic trial in bronchiectasis reduced exacerbations by 39%.^4^

For 90% power (two-sided 5% significance level) to conclude that LAMA/LABA is more effective than placebo with the above parameters, we have calculated (assuming large-sample approximation of the Poisson distribution) that a sample size of 600 participants is needed, randomised 240:240:120 between LAMA/LABA, ICS/LAMA/LABA and placebo. This allows for a 5% loss to follow-up. This represents a conservative retention rate compared with over 95% observed in the NIHR *HTA* TWICS study with similar pragmatic design and limited patient burden. This calculation assumes a difference between placebo and LABA/LAMA of 0.5 exacerbations per year (21% relative reduction).

If superiority of LAMA/LABA versus placebo is concluded, we will then test non-inferiority of LAMA/LABA against ICS/LAMA/LABA. The sample size will give 90% power (one-sided 5% type I error) with a 0.38 non-inferiority margin (reflecting 20% of the assumed LAMA/LABA rate).

In the early stages of the trial, it was found that exacerbation rates in prebaseline periods were lower than they had been historically, mostly due to the presumed effect of COVID-19 restrictions. The inclusion criteria were therefore updated in protocol V.5.0 (see Amendments). A recalculation of the power of the trial was conducted assuming that there would be lower exacerbation rates in the follow-up period. We assumed that the placebo exacerbation rate would be an average of 1.9 per year. We recalculated the power for two scenarios: (1) assuming that the same absolute difference (0.5) between LAMA/LABA versus placebo and the same non-inferiority margin (0.38) as previously; (2) the same relative difference (21%) between LAMA/LABA vs placebo and relative non-inferiority margin (20%) as before. Table 4 shows the power of the trial to conclude non-inferiority and superiority.

**Table 4 T4:** Power calculations

Scenario	Mean exacerbation rate			NI margin (relative to active control)	Power*	
	Placebo	ICS/LAMA/LABA (intervention)	LAMA/LABA (active control)		Non-inferiority (%)	Superiority (%)
Presented in original grant application	2.4	1.9	1.9	0.38 (20%)	90.3	89.8
Updated inclusion criteria (same absolute differences)	1.9	1.4	1.4	0.38 (26.7%)	96.3	95.8
Updated inclusion criteria (same relative differences)	1.9	1.5	1.5	0.3 (20%)	83.4	83.4

*Note this is assuming analytical formulae, with simulations giving consistent but slightly higher powers.

ICS, inhaled corticosteroid; LABA, long acting beta agonist; LAMA, long acting muscarinic antagonist; NI, non-inferiority.

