### Analysis

#### Analysis of the primary outcome measure

The primary outcome—number of bronchiectasis exacerbations per participant requiring antibiotics over 12 months—will be compared between randomised groups using negative binomial regression adjusted for stratification factors. This model will be used to compute CIs to test the superiority and non-inferiority hypotheses. The two-sided 95% CI for difference in mean number of exacerbations per year between the combination of LAMA/LABA and ICS/LAMA/LABA compared with placebo will be found: the placebo versus LAMA/LABA hypothesis will be rejected if the upper limit is lower than 0. We will estimate the difference between LAMA/LABA and ICS/LAMA/LABA arms on the relative scale using the incidence rate ratio, and test whether the upper boundary of the two-sided 90% CI is lower than 1.2. We will consider the time at risk to be the time not spent in exacerbation (so that while a patient is in an exacerbation, they are not included as at risk for another).

A secondary analysis will define the at-risk time as the entire length of follow-up for the patient. Estimates will then be adjusted for sites, the stratification factors and other baseline covariates that are known to be strongly related to outcome (eg, age, smoking, bronchiectasis hospitalisations in year prior to trial—these will be prespecified in the Statistical Analysis Plan (SAP)).

We will undertake a sensitivity analysis by excluding those participants who have died. If there is any indication of a differential effect on deaths by treatment, we may consider models that allow the censoring to be informative. For participants who are lost to follow-up by 12 months, their information will be included in the statistical models up to the point that they are lost to follow-up. If loss to follow-up is higher than 10% we will conduct sensitivity analyses to investigate the impact.

We will also explore time to first exacerbation using a Cox regression, and a recurrent events analysis to allow for subsequent exacerbations. In addition, we will use mortality and hospitalisations due to bronchiectasis exacerbation data collected up until 24 months to extend the modelling beyond 12 months as a sensitivity analysis.

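### The superiority power in Table 4 (89.8%, 95.8%, 83.4%) is not that of the stated two-sided 5% test of LAMA/LABA versus placebo, which is about 83%, 91% and 75%

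*Protocol article*

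**What the plan says.** The section Sample size calculations ties the power claim to one comparison and one level: "For 90% power (two-sided 5% significance level) to conclude that LAMA/LABA is more effective than placebo with the above parameters". For placebo it "assumed a mean of 2.4 over 1 year". It takes 1.9 per year in both active arms, a difference of 0.5. The method is described as "assuming large-sample approximation of the Poisson distribution". The sample is 600, "randomised 240:240:120 between LAMA/LABA, ICS/LAMA/LABA and placebo", and the text says this allows for 5% loss to follow-up. A one-sided 5% error rate appears only for the later non-inferiority test.

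After eligibility was widened, power was recalculated for a placebo rate of 1.9, and "Table 4 shows the power of the trial to conclude non-inferiority and superiority". The superiority column reads 89.8% (2.4 v 1.9), 95.8% (1.9 v 1.4) and 83.4% (1.9 v 1.5). The table's footnote says these come from analytical formulae and that simulations gave slightly higher values.

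The section Analysis of the primary outcome measure decides superiority from a two-sided 95% CI: "the placebo versus LAMA/LABA hypothesis will be rejected if the upper limit is lower than 0".

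**The concern.** A two-sided 5% test, or equivalently a two-sided 95% CI lying wholly below zero, uses a critical value of 1.96. With the stated rates and numbers, that value gives visibly less than 90% power, and all three printed figures are too high by several points.

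This is the power of the primary test, and non-inferiority of LAMA/LABA to triple therapy is tested only if superiority over placebo is concluded. Table 4 is also the evidence that the trial stayed adequately powered once exacerbation rates fell. It shows every superiority figure above 83%, when one is below 75%. A null result would be read against a power that the design does not have.

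**Working it through.** **Inputs** (Sample size calculations and Table 4): Poisson counts over one year, so variance equals mean; 240 v 120 less 5% = 228 v 114; rate pairs 2.4 v 1.9, 1.9 v 1.4 and 1.9 v 1.5; two-sided 5%, z = 1.960.

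**Step 1: check the formula on the plan's non-inferiority column.** Equal rates r in both active arms, margin m, 228 per arm, one-sided 5%: power = Φ(m / √(2r/228) − 1.645).

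- r = 1.9, m = 0.38: SE 0.1291, ratio 2.943, power 90.3% (printed 90.3%)
- r = 1.4, m = 0.38: SE 0.1108, ratio 3.429, power 96.3% (printed 96.3%)
- r = 1.5, m = 0.30: SE 0.1147, ratio 2.615, power 83.4% (printed 83.4%)

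All three agree to the decimal. In that column, therefore, the method is a difference in rates with unpooled Poisson variance, with the 5% loss applied.

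**Step 2: apply the same formula to superiority.** Power = Φ((p − a) / √(p/114 + a/228) − z).

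| Scenario | SE | (p − a)/SE | z = 1.960 | z = 1.645 | Table 4 |
|---|---|---|---|---|---|
| 2.4 v 1.9 | 0.1714 | 2.917 | 83.1% | 89.8% | 89.8% |
| 1.9 v 1.4 | 0.1510 | 3.311 | 91.2% | 95.2% | 95.8% |
| 1.9 v 1.5 | 0.1525 | 2.624 | 74.7% | 83.6% | 83.4% |

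With the third active rate taken as 1.9 × 0.79 = 1.501, the last row becomes 74.4% (two-sided) and 83.4% (one-sided). The shortfalls at the stated level are 6.7, 4.6 and 8.7 points.

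**Step 3: try other two-sided forms of the same comparison.** Log rate ratio, two pooled-variance forms and the square-root scale reach at most 85.8 / 93.6 / 77.9% with the loss applied. Ignoring the loss, they reach at most 87.5 / 94.7 / 79.9%, and the unpooled difference gives 84.9 / 92.5 / 76.8%. Poisson simulation with the loss, on the difference and log scales, gives 83.6–84.8 / 92.0–92.8 / 74.1–75.9% (third active rate 1.504). A non-standard form that uses the lower, active rate as the variance in both arms gives 88.5 / 95.8 / 81.3% with the loss and about 90.0 / 96.6 / 83.2% without it. It understates the placebo variance and in neither case matches all three figures.

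**Step 4: sample size for 90% in the first scenario.** Evaluable placebo n = (2.4 + 1.9/2) × (1.960 + 1.2816)² / 0.5² = 140.8, rounded up to 141. The total at 2:2:1 with 5% loss is 141 × 5 / 0.95 ≈ 742. The same formula at one-sided 5% gives 114.8 × 5 / 0.95 ≈ 604, close to the 600 chosen.

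**The case against.** The strongest objection is that the contrast itself is unclear. In the Analysis section, the first part of the sentence that sets the two-sided 95% CI speaks of the two active regimens in combination, compared with placebo. Read literally, that pools both active arms. At two-sided 5% the pooled contrast comes close to Table 4: 480 v 120 without loss gives 89.8 / 95.5 / 82.8%. With loss (456 v 114) the result runs from 88.3 / 94.5 / 80.8% (unpooled variance) to 90.3 / 96.1 / 83.4% (simple average rate as common variance) and somewhat higher on other forms. The one-sided account also misses the second row, 95.2% against 95.8%. Pooling therefore explains the figures about as well.

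What stands is that the cause is an inference. Neither account reproduces every figure exactly from one set of inputs, and the wording of the contrast needs tidying. What does not stand is the use of pooling to support the printed power. The 90% sentence names LAMA/LABA versus placebo, the recalculated scenarios are defined for that contrast, and the rejection rule at the end of the same Analysis sentence names it too.

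The footnote on simulations does not help, since it says the printed values are analytical. It is also fair to say that type I error is not affected and that, with recruitment closed (Trial status), the 742 cannot change the design.

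**Conclusion.** The concern holds. For LAMA/LABA versus placebo at two-sided 5%, with 5% loss and Poisson variance, power is 83.1%, 91.2% and 74.7% against the printed 89.8%, 95.8% and 83.4%. The range over standard approximations is 83.1–85.8%, 91.2–93.6% and 74.7–77.9%. The type II error in the same-relative-difference scenario is about 25% (100 − 74.7), not 17% (100 − 83.4). The most likely explanation is a one-sided 5% critical value, but the conclusion does not depend on it.

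Poisson variance is the favourable case. The planned analysis is negative binomial, and any overdispersion would lower power further. No dispersion value is given, so that is not quantified here.

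**What to change.** Replace the superiority column of Table 4 with 83.1%, 91.2% and 74.7%, or re-run the simulations at two-sided 5% for 228 v 114 and report those results with the method named. Change the 90% claim in Sample size calculations to about 83%. Keep the two-sided 95% CI as the decision rule; moving to a one-sided test to fit the table would weaken the primary test. In the same edit, reword the Analysis sentence so that the contrast is unmistakably LAMA/LABA versus placebo, matching its own rejection rule and the sample size text.

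The cost is a correction to text and one table, and a less favourable stated power. No extra patients and no change to the analysis are needed.

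### The stated non-inferiority powers (90%; Table 4: 90.3, 96.3 and 83.4%) are stand-alone test powers, presented as the trial's power to conclude a hypothesis that is tested only after superiority over placebo

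*Protocol article*

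**What the plan says.** All of this is in the protocol article under Sample size calculations.

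- **Order of testing:** "If superiority of LAMA/LABA versus placebo is concluded, we will then test non-inferiority of LAMA/LABA against ICS/LAMA/LABA".
- **Power of the second step:** the next sentence reads "The sample size will give 90% power (one-sided 5% type I error) with a 0.38 non-inferiority margin".
- **Power of the first step:** "For 90% power (two-sided 5% significance level) to conclude that LAMA/LABA is more effective than placebo", calculated "assuming large-sample approximation of the Poisson distribution".
- **Size and allocation:** "a sample size of 600 participants is needed, randomised 240:240:120 between LAMA/LABA, ICS/LAMA/LABA and placebo", and "This allows for a 5% loss to follow-up".
- **Table 4:** it is introduced with "Table 4 shows the power of the trial to conclude non-inferiority and superiority". Non-inferiority power is 90.3, 96.3 and 83.4% for the three scenarios. Superiority power, in the adjacent column, is 89.8, 95.8 and 83.4%. A footnote says the figures come from analytical formulae and that simulation gave slightly higher values.

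The article gives no joint power and does not say whether the non-inferiority column allows for the first step.

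**The concern.** In a fixed sequence the second hypothesis can be concluded only when both tests succeed. The power to conclude it is therefore a joint probability and cannot exceed the power of the first step. In the first two rows of Table 4 the non-inferiority figure is above the superiority figure in the same row (90.3 against 89.8; 96.3 against 95.8). No gated test can have that property, so the column cannot be what its introduction says it is.

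Dual against triple therapy, that is, whether the inhaled corticosteroid adds anything, is one of the trial's two formal hypotheses. The recalculation after the eligibility change exists to show what power remains. A reader of the third row sees 83.4% and infers about a 17% chance of not concluding non-inferiority when the assumptions hold. Under the planned sequence that chance is materially larger, and part of it arises only because the placebo step fails.

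**Working it through.** **Inputs.** From Sample size calculations and Table 4: 240:240:120 less 5% gives 228, 228 and 114 evaluable. Rates (placebo / each active arm) and margins are 2.4 / 1.9, margin 0.38; 1.9 / 1.4, margin 0.38; 1.9 / 1.5, margin 0.3. Counts are Poisson with a normal approximation on the difference scale. Non-inferiority is one-sided 5% (1.645); superiority is two-sided 5% (1.96).

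**Step 1: reproduce the stated non-inferiority powers.** Power = Φ(margin / √(2 × rate / 228) − 1.645).

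- Row 1: 0.38 / 0.1291 = 2.943; less 1.645 = 1.298; power 90.3%.
- Row 2: 0.38 / 0.1108 = 3.429; less 1.645 = 1.784; power 96.3%.
- Row 3: 0.30 / 0.1147 = 2.615; less 1.645 = 0.970; power 83.4%.

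All three agree with Table 4 to the decimal. Nothing in the formula refers to the superiority test.

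**Step 2: correlation between the two tests.** The LAMA/LABA arm enters both contrasts. In each, a low LAMA/LABA rate favours success, so the correlation is positive:

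ρ = (active rate / 228) / (SE of superiority contrast × SE of non-inferiority contrast), where SE of superiority = √(active rate / 228 + placebo rate / 114).

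For row 1 the superiority SE is √(0.00833 + 0.02105) = 0.1714, so ρ = 0.00833 / (0.1714 × 0.1291) = 0.377. Rows 2 and 3 give 0.367 and 0.376.

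**Step 3: joint power from the printed powers.** This is the bivariate normal probability with both printed powers as margins and the ρ above.

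| Row | Superiority, printed | Non-inferiority, printed | Joint | Points below the printed non-inferiority power |
|---|---|---|---|---|
| 1 | 89.8% | 90.3% | 82.6% | 7.7 |
| 2 | 95.8% | 96.3% | 92.7% | 3.6 |
| 3 | 83.4% | 83.4% | 72.3% | 11.1 |

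**Step 4: joint power with superiority at the stated level.** Pairwise superiority power = Φ(difference / SE of superiority − 1.96).

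- Row 1: 0.5 / 0.1714 = 2.917; less 1.96 = 0.957; 83.1%.
- Row 2: 0.5 / 0.1510 = 3.311; less 1.96 = 1.351; 91.2%.
- Row 3: 0.4 / 0.1525 = 2.624; less 1.96 = 0.664; 74.7%.

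These are below the printed superiority powers. Using 1.645 instead gives 89.8, 95.2 and 83.6%, close to the printed column. With the two-sided values, joint power is 77.0, 88.5 and 65.7%, which is 13.3, 7.8 and 17.7 points below the printed non-inferiority powers.

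**Step 5: simulation.** Poisson simulation of the pairwise gate at two-sided 5% (400,000 runs per scenario) gave joint power 77.9, 89.4 and 66.7%. With a one-sided 5% gate it gave 83.4, 92.7 and 73.4%. Stand-alone non-inferiority power stayed at 90.3, 96.3 and 83.5%. The footnote on simulation therefore does not close the gap.

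**Step 6: could the column be conditional power?** Joint divided by printed superiority power is 92.0, 96.8 and 86.7%. These are not the printed figures.

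**The case against.** The strongest reply is that quoting a separate power for each step of a hierarchy is common practice. The gate is stated in the sentence just before the 90%, the two tests have separate columns, and a careful reader who sees non-inferiority power above superiority power can work out that the column is per test. Read as the power of the non-inferiority test itself, every figure is right, and as power conditional on passing the gate the figures are slightly conservative (Step 6). Nothing in design, conduct or error control depends on the label, and recruitment has closed.

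Most of that stands. There is no arithmetic error in the non-inferiority column, and the consequence is limited to how the power is described. What does not stand is that the text makes the meaning clear. It presents the figures as the trial's power to conclude non-inferiority, neither labels them stand-alone nor gives a joint value, and in two rows prints a number that the stated procedure cannot reach.

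A reader might also infer a loss of 4 to 14 points by multiplying the two printed powers (81.1, 92.3 and 69.6%). Multiplication assumes uncorrelated tests, which would suit a gate comparing both active arms pooled with placebo. The Analysis section can be read that way, but Sample size calculations names LAMA/LABA against placebo, and that contrast shares an arm with the non-inferiority test. The 14-point end is therefore not supported by the gate as stated.

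**Conclusion.** The point holds as a misdescription of power. The stated 90% and the Table 4 values are correct for a stand-alone test and overstate the chance that the planned sequence concludes non-inferiority. With the printed powers taken at face value and the stated gate, that chance is about 82.6, 92.7 and 72.3%. With a pairwise two-sided 5% gate and 228 against 114 evaluable, it is about 77.0, 88.5 and 65.7%. The direction is certain. The size depends on which superiority contrast and critical value are used, and row 2 loses under 4 points on the printed powers.

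These values assume Poisson counts, equal active-arm rates, 5% loss and the difference-scale margin, as Table 4 does. They also assume that a lower LAMA/LABA rate favours both tests, as in the text. Table 4 labels the triple arm as intervention and the dual arm as active control. If non-inferiority ran in that direction, the correlation would be negative and the loss on the printed powers would be 10.0, 4.2 and 15.7 points.

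A reader might go further and conclude that the trial is too small or that the test order is wrong. The documents do not support either: the sequence is legitimate, and only the description of its second-step power is at fault.

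**What to change.** Label the non-inferiority column of Table 4, and the sentence giving 90% power, as *stand-alone non-inferiority test, ignoring the superiority gate*. Add beside it the joint power, meaning the probability that superiority and then non-inferiority are both concluded.

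Do not simply print the 82.6, 92.7 and 72.3% above. They rest on superiority powers that the stated pairwise two-sided 5% test does not reproduce. Check those first, confirm which contrast forms the gate and at what level, and then compute the joint figure from that.

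The cost is one bivariate normal or simulation calculation and a change of wording. Sample size and test order stay as they are. The only downside is that the stated power becomes less favourable.
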